# Combining Noninvasive Brain Stimulation and Physiotherapy to Improve the Management of Chronic Low Back Pain in Veterans: Protocol for a Multi-Arm Randomized Controlled Trial

**DOI:** 10.2196/78952

**Published:** 2026-01-26

**Keywords:** low back pain, chronic pain, rehabilitation, transcranial magnetic stimulation, psychosocial, physiotherapy, military

## Abstract

**Background:**

Low back pain (LBP) is the most common chronic pain condition in veterans, but the effectiveness of standard management approaches is modest. Addressing the psychological risk factors of chronic pain that are often observed in this population (eg, anxiety, depression, stress and mood disorders) may be important to enhance outcomes. Psychologically informed physiotherapy (PiP) identifies and mitigates the negative impacts of emotional and cognitive factors alongside the biomedical aspects of chronic LBP to improve physical functioning and has shown promising results in this population. However, residual pain and disability often persist in veterans. The combination of PiP with repetitive transcranial magnetic stimulation (rTMS) to the prefrontal cortex may enhance its effectiveness by modulating cognition, emotion, and pain perception.

**Objective:**

The aim of this study is to compare the effects of (1) combining active rTMS with PiP, (2) combining sham rTMS with PiP, and (3) usual physiotherapy (UP) on physical functioning in veterans with chronic LBP and comorbid psychological risk factors. Secondary objectives include comparing their effect on pain intensity, quality of life, depression symptoms, pain catastrophizing, movement pain–related fear, self-efficacy, medication use, and posttraumatic stress disorder symptoms.

**Methods:**

Ninety-six veterans with chronic LBP and comorbid psychological risks factors of pain will be enrolled in this 3-arm parallel randomized controlled trial. Individuals will be allocated to receive an 8-week intervention of (1) active rTMS + PiP, (2) sham rTMS + PiP, or (3) UP. Online self-administered questionnaires will be completed at baseline, 2, 8, and 26 weeks after the first treatment session. A linear mixed model will be used to assess the treatment effects by using intention-to-treat analyses. We hypothesize that active rTMS + PiP will be more effective than sham rTMS + PiP and that active PiP + rTMS or sham rTMS will be more effective than UP.

**Results:**

Ethics approval was obtained in January 2025, and participating physiotherapists completed the 2-day PiP training in May 2025. Participants have been recruited since June 2025. As of December 2025, 28 participants have been included, and recruitment is expected to continue up to June 2027, targeting the inclusion of approximately 4 new participants per month. Follow-up should be completed by December 2027, and results will be analyzed. The results of this randomized controlled trial should be published and available in June 2028.

**Conclusions:**

It is paramount to identify innovative and effective interventions for the management of chronic LBP in veterans. This study will provide new evidence on the effectiveness of two innovative interventions targeting cognitive and emotional factors of pain (ie, PiP and rTMS). If our hypothesis is confirmed, it could motivate changes in clinical practice and improve the quality of life of veterans living with chronic LBP.

**Trial Registration:**

ClinicalTrials.gov NCT06999772; https://clinicaltrials.gov/study/NCT06999772

**International Registered Report Identifier (IRRID):**

PRR1-10.2196/78952

## Introduction

Chronic low back pain (CLBP) stands as the leading cause of years lived with disability globally [1,2]. Addressing this widespread chronic condition poses a notable challenge to both the public and military health care systems. The effectiveness of standard management approaches for CLBP has been found to be modest in both general [3] and military/veteran [4,5] populations, further negatively impacting the quality of life of these people.

In military veterans, CLBP is the most prevalent painful condition [6,7], with prevalence rates reaching 45% [7]. Moreover, veterans are more likely to experience more severe pain intensity and pain-related disability than the civilian population [8]. The poor response to current interventions in this highly impacted population exacerbates the current opioid crisis [9], urging the need for new, effective, and noninvasive interventions.

The limited effectiveness of current interventions suggests that they may not adequately target specific mechanisms underlying CLBP. In the last few years, a paradigm shift has been noted in CLBP management, transitioning from a strictly biomedical perspective to a more comprehensive biopsychosocial approach [10]. Moreover, our understanding of the mechanisms of CLBP has evolved. For example, evidence reveals abnormal brain functioning among individuals with CLBP [11], suggesting the involvement of alterations within the central nervous system in certain people [12]. As the painful symptoms persist, a shift from circuits processing nociceptive inputs to circuits processing emotional states may occur in those at the highest risk to develop chronic pain [13,14]. The corticolimbic system (including the prefrontal cortex [PFC] and limbic system), which is critical in the regulation, processing, and control of emotions, plays a significant role in the inhibition of pain through cognitive control mechanisms within the cortex [14]. Enhanced cognitive and emotional valuation of pain may act as an amplifier of nociception [14]. This transition aligns with the identified multidimensional factors contributing to chronicity [15].

Psychological disorders like depression and anxiety and factors like pain catastrophizing, and movement pain–related fear have repeatedly been linked to the persistence of LBP and long-term disability [16,17]. These psychological factors represent higher-order cognitive and emotional processes occurring, *inter alia*, within the PFC [18], and alterations in brain processing may exacerbate nociception and contribute to the persistence of pain. This physiological phenomenon is referred to as nociplastic pain mechanisms [19]. Considering that psychological factors are more prevalent among veterans compared to civilians [7,20] and are associated with the emergence of chronic pain in this population [7,20-22], there might be a critical need for interventions identifying and mitigating these factors [23]. However, they are frequently overlooked in standard health care practices [24,25].

Usual physiotherapy (UP) constitutes a standard health care intervention for veterans experiencing LBP, and although being effective to improve symptoms and disability compared to no intervention, it often fails to consider the psychological prognostic factors of persistent pain. Psychologically informed practice utilizes a biopsychosocial approach to recognize and address emotional and cognitive components associated with the condition, using different therapeutic modalities such as education, gradual exposure to movement, and stress management strategies [26]. When delivered by physiotherapists combined with UP care, the psychologically informed practice is called psychologically informed physiotherapy (PiP) [26]. PiP represents a promising intervention for the management of CLBP, especially in veterans, as it targets the highly prevalent psychological factors present in this population. This approach is currently supported by evidence from civilian populations: meta-analyses have shown that integrating psychological interventions with UP leads to greater improvements in pain intensity and physical functioning in people with CLBP [27], including those presenting comorbid psychological factors [28], when compared to UP alone.

In addition to PiP, noninvasive brain stimulation over the PFC by using repetitive transcranial magnetic stimulation (rTMS) may be useful to modulate the cognitive and emotional processing involved in pain mechanisms [29,30]. This approach is supported by large randomized controlled trials in psychiatric populations [29]. rTMS depolarizes neurons under the stimulating coil, and modulates brain excitability [31], leading to changes in network connectivity [29] that have been linked to reductions in symptoms such as rumination and negative bias [29,31]. Through potential similar mechanisms, rTMS over the PFC has been shown to reduce pain intensity in cases of neuropathic pain [32], a finding that may relate to the high prevalence of psychological comorbidities among people with chronic pain [16,17]. To date, most studies that have investigated the use of rTMS for chronic musculoskeletal pain stimulated the motor cortex (M1), yielding conflicting results [33-35]. Stimulating the PFC could optimize results by targeting brain areas specifically involved in pain modulation. A pilot randomized controlled trial (RCT) (n=20) studied the efficacy of noninvasive brain stimulation over a prefrontal cortical area in veterans with CLBP, and this stimulation resulted in a large improvement in the physical functioning and depressive symptoms compared to a placebo [36]. PiP and rTMS are two promising interventions specifically targeting psychological factors and cortical mechanisms contributing to CLBP in veterans. Despite these promising pilot results, good quality RCTs investigating the effectiveness of rTMS over the PFC for chronic LBP are still needed.

PiP and rTMS are two promising interventions specifically targeting psychological factors and cortical mechanisms contributing to CLBP in veterans. Combining psychologically informed clinical intervention to rTMS could enhance treatment outcomes, as they could both modulate cognitive and emotional processing involved in pain mechanisms, through different pathways [29]. However, the combination of these two interventions has never been studied in chronic musculoskeletal pain and compared to usual care.

Therefore, the main objective of this study will be to compare the effectiveness of (1) combining PiP + active rTMS, (2) PiP + sham rTMS, and (3) UP alone in improving the physical functioning in veterans experiencing CLBP and comorbid psychological factors. The secondary objectives will be to compare their effectiveness on pain intensity, quality of life, movement pain–related fear, pain catastrophizing, self-efficacy, depressive symptoms, medication use, and posttraumatic stress disorder symptoms. We hypothesize that the combination of active rTMS + PiP will result in a larger effect on primary and secondary outcomes compared to PiP + sham rTMS and UP alone. In addition, we hypothesize that PiP with active rTMS or sham rTMS will be more effective than UP.

## Methods

### Study Design

This protocol is reported according to the SPIRIT (Standard Protocol Items: Recommendations for Interventional Trials) guidelines [37]. Participants included in this 3-arm, parallel-group RCT will be randomized to one of the 3 groups (PiP + active rTMS, PiP + sham rTMS, or UP) and will undergo an 8-week intervention. Outcomes measurements will occur at baseline, 2, 8, and 26 weeks after the beginning of the intervention (Figure 1). The protocol of this RCT has been registered on ClinicalTrials.gov (NCT06999772).

**Figure 1 figure1:**
[figure not shown]
Flowchart of the participants. PiP: psychologically informed physiotherapy; rTMS: repetitive transcranial magnetic stimulation; UP: usual physiotherapy.

### Ethical Considerations

Ethics approval has been granted by the Comité d’éthique de la Recherche Sectoriel en Réadaptation et Intégration Sociale du CIUSSS de la Capitale-Nationale (Rehabilitation and Social Integration section; 2025-3215). All participants will provide a written informed consent prior to their participation in the study and will be free to opt out whenever they wish to. Participants will receive compensation of CAD $40 (US $29) after the first 4 weeks of treatment and CAD $40 (US $29) after the last 4 weeks to offset the costs incurred for traveling to appointments. In addition, CAD $20 (US $15) will be given to participants who complete their 6-month follow-up questionnaires in order to increase the retention rate. All collected data using REDCap will be deidentified, and any participant information at recruitment will be kept on an online spreadsheet secured with a password. Only members in the research team have access to this information.

### Randomization and Blinding

A randomization list will be generated using a computer random number generator by blocks of 3, 6, or 9 by an independent research assistant. The randomization list will be uploaded on a Research Electronic Data Capture (REDCap, Vanderbilt University) platform by using the randomization module. Once the randomization list will be uploaded, REDCap will automatically retrieve the group allocation. This method digitally replicates the allocation concealment and prevents selection bias without having to manipulate sealed envelopes. Randomization will be stratified by self-reported gender and physical functioning (ODI score ≤ or > 40).

To ensure that no assessor could bias data collection, all patient-reported outcome measures (PROMs) will be assessed using REDCap. Although it is not possible to blind participants to a physical intervention (UP and PiP), they will be blinded to rTMS group allocation (active vs sham). The rTMS intervention will be delivered at the research center, and the physiotherapy interventions will be delivered in local physiotherapy clinics. The 2 interventions (PiP or UP) will be provided in 2 different physiotherapy clinics, reducing the risks of potential group contamination. Furthermore, the physiotherapists providing PiP will not be informed of the type of rTMS (sham vs active), and participants will be asked not to discuss rTMS sessions with their treating physiotherapist. The statistician will be blinded to group allocation. Overall, the RCT will be triple-blind for rTMS (ie, participants, treating physiotherapist, statistician) and single-blind for physiotherapy (ie, statistician). At week 8, participants in the PiP groups will be asked to determine which stimulation they believed they received (sham, active, or don’t know) and to provide the reasons for their choice through a blinding evaluation questionnaire. At any time during the trial, if any severe adverse event occurs (ie, seizure), the research team and the participant will be informed of its group allocation to appropriately manage this event.

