**Figure 3 figure3:**
[figure not shown]
Intervention timelines for the usual care group. Each bar represents a physiotherapy session provided in one of the participating local clinics. In the first 4 weeks, 4 sessions were offered at 1-week interval. In the last 4 weeks of the intervention, 2 additional sessions were offered at 2-weeks interval.

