#### PiP Intervention

The objective of PiP is to identify the biopsychosocial factors that may impede recovery and to address these factors within the physiotherapy scope of practice. To standardize PiP delivery, treating physiotherapists providing PiP will receive a 2-day training provided by an expert in PiP who also has expertise with military personnel. They will learn to use strategies such as the establishment of common goals and therapeutic alliance, the use of the behavior change model, motivational interviewing approach, education on pain neuroscience, gradual exposure to movement, and stress management strategies (eg, breathing techniques, meditation) [45]. The training will also include a section on the military culture to foster therapeutic alliance with veterans and optimize the treatment adherence. It provides foundational knowledge about the Canadian Armed Forces, including its branches, core values, and professional expectations. It supports participants in understanding how military culture influences health behaviors and offers guidance on how this awareness can inform clinical assessments and interventions with veterans. These physiotherapists will also be allowed to use standard physiotherapy modalities presented in the UP section, based on their clinical judgement. However, they will be encouraged to assess and address psychosocial factors by using strategies learned during their training. This training has been shown to be effective in leading to changes in the clinical practice of physiotherapists, leading to a greater use of modalities targeting psychological factors compared to UP [45]. Participants in the PiP + active rTMS and PiP + sham rTMS groups will have access to a website offering support information on topics such as pain neuroscience education, common myths and misconceptions about back pain, the psychological factors influencing pain, self-management strategies, and healthy lifestyle habits (eg, sleep and nutrition). This site will be freely available to participants during the study. Physiotherapists will be asked to discuss one topic at each session with the participants to assess and reframe (if necessary) their conceptualization of these concepts.

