#### UP Intervention

This pragmatic group aims to represent real-world clinical practice, including interventions commonly used in physiotherapy to manage CLBP. No training will be provided, and all modalities typically used by physiotherapists in the province of Quebec will be allowed, including but not limited to manual therapy, active exercises, education, stretching, etc. Each physiotherapy session, including PiP and UP, will last between 30 and 45 minutes. Physiotherapists providing UP and PiP will all complete a checklist to indicate the interventions provided at each treatment session.

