#### Analysis

##### Sample Size Calculation

The trial is designed to detect a 9-point (SD 10) between-group difference in physical functioning at 8 weeks, as measured using the minimal important difference of the ODI [54]. The standard deviation was estimated from our previous RCTs [45,55]. Considering 20% loss at follow-up, 1-β=.90, and α=.05, 32 participants per group will be recruited (n_total_=96).

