#### Statistical Analysis

A linear mixed model will be used to compare treatment effects on outcomes, using intention-to-treat analyses. Group (active rTMS + PiP, sham rTMS + PiP, and UP) and time (baseline, 2, 8, 26 weeks) will be entered as fixed factors, participants as random intercept, and stratification factors (gender and baseline ODI score) as covariate, to determine the presence of any significant group × time interaction. Missing values will be handled with multiple imputations if necessary, and sensitivity analyses will be completed to confirm/infirm the results.

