Some limitations should, however, be mentioned. First, the optimal parameters for rTMS treatment over the PFC are still unknown. The parameters for this study are based on available evidence, which has mainly been conducted in patients with neuropathic pain [62-64]. It is possible that they are not optimal for the treatment of CLBP. Second, based on evidence from the population with depression, the use of psychotropic medication may attenuate the treatment response to rTMS [65]. We anticipate a high prevalence of psychotropic medication use among our participants, given the elevated rates of psychological disorders observed in veteran populations [7,20]. Finally, several clinicians will be providing care for whom PiP is a new concept. As such, it is possible that the standardization of the PiP intervention may be suboptimal despite the two days of training provided. To optimize standardization and application of the concepts, clinicians will be able to contact the expert clinician who provided the training throughout the study to validate information about the intervention provided. In addition, clinicians’ logbooks will allow us to see which interventions were used with participants.

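### The planned model has no physiotherapist effect, so if outcomes after treatment starts cluster by therapist, the standard errors of both PiP-versus-UP contrasts are too small

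*Protocol article*

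**What the plan says.** Under Randomization and Blinding, the article separates the two physiotherapy approaches by site: "The 2 interventions (PiP or UP) will be provided in 2 different physiotherapy clinics, reducing the risks of potential group contamination". Under PiP Intervention, "treating physiotherapists providing PiP will receive a 2-day training provided by an expert in PiP"; under UP Intervention, "No training will be provided, and all modalities typically used by physiotherapists in the province of Quebec will be allowed". The article does not say in so many words that the two sets of physiotherapists are distinct, but separate sites and PiP-only training leave little other reading.

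The number of sites is less clear. The Figure 3 legend says of the usual-care arm: "Each bar represents a physiotherapy session provided in one of the participating local clinics", which could mean more than one UP clinic.

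The Statistical Analysis section names group and time as fixed factors, with "participants as random intercept, and stratification factors (gender and baseline ODI score) as covariate", and tests the group × time interaction. Baseline is one of the time levels. No therapist or clinic term appears. The Sample Size Calculation section makes no allowance for clustering: "The trial is designed to detect a 9-point (SD 10) between-group difference in physical functioning at 8 weeks".

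The limitations in the Discussion acknowledge that "several clinicians will be providing care for whom PiP is a new concept" and that PiP delivery may not be fully standardized. They do not mention correlated outcomes within therapist, or that clinic and approach go together.

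**The concern.** Patients treated by the same physiotherapist tend to share part of their outcome. When each therapist delivers only one approach, that shared part does not cancel between PiP and UP: it adds variance to the difference that a participant-only random intercept treats as if it averaged out over independent patients. The article itself gives reason to expect such variation. Clinicians are new to PiP, PiP therapists may add usual modalities at their own judgement, and UP therapists may use any customary modality.

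Two of the three hypothesized comparisons are affected, namely each PiP arm against UP. The Discussion says that superiority of PiP over UP could motivate clinicians to train in PiP, so the precision of these contrasts matters. Active versus sham is in a different position: if the same PiP therapists treat both arms, their effects largely cancel.

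**Working it through.** **1. The plan's own sample size.** Inputs: difference 9, SD 10, α = 0.05 (two-sided assumed), power 0.90, 20% loss. n = 2 × (1.96 + 1.2816)² × 10² / 9² = 25.9, so 26 evaluable per arm. Inflation gives 26 / 0.8 = 32.5 (33) or 26 × 1.2 = 31.2 (32). The stated 32 per group reproduces, with every patient treated as independent.

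**2. Assumed clustering inputs (not in the article).** Caseload of 8 evaluable patients per therapist; ICC of 0.02, 0.05 or 0.10 for outcomes after treatment starts. PiP therapists serve two arms, so about 4 of their 8 patients fall in each PiP arm. A UP therapist's 8 patients are all in the UP arm.

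**3. Design effect of a PiP-arm-versus-UP contrast.** PiP arm: 1 + (4 − 1) × ICC. UP arm: 1 + (8 − 1) × ICC. With equal arm sizes the contrast takes the mean, 1 + 5 × ICC.

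**4. Consequences.** With 32 × 0.8 = 25.6 evaluable per arm, the standardized effect is 0.9 × √(25.6/2) = 3.22. DE is the design effect.

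- Type I error of the planned test: 2 × [1 − Φ(1.96/√DE)]
- Power of a correctly adjusted test: Φ(3.22/√DE − 1.96)
- Chance that the planned, unadjusted test rejects at 9 points: Φ((3.22 − 1.96)/√DE)

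| ICC | DE | Type I error, planned test | Power, adjusted test | Rejection at 9 points, planned test |
|---|---|---|---|---|
| 0.02 | 1.10 | 6.2% | 87% | 89% |
| 0.05 | 1.25 | 8.0% | 82% | 87% |
| 0.10 | 1.50 | 11.0% | 75% | 85% |

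The last column shows that the planned test itself would lose little apparent power. Its fault is excess false positives.

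**5. Dependence on therapist numbers.** With 26 per arm and k equal-caseload therapists per approach, Var = 100 × [(1 − ICC) × 2/26 + ICC × (2/k)]. The independent-patients SE is √(100 × 2/26) = 2.77 ODI points.

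| ICC | k per approach | SE | Ratio to 2.77 |
|---|---|---|---|
| 0.01 | 4 | 2.85 | 1.03 |
| 0.05 | 8 | 2.93 | 1.05 |
| 0.05 | 4 | 3.13 | 1.13 |
| 0.05 | 2 | 3.51 | 1.26 |
| 0.05 | 1 | 4.16 | 1.50 |

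The normal approximation is optimistic with few therapists. At ICC 0.05 and k = 4, power is 0.82 by the normal approximation but 0.67 with a t critical value on 4 + 4 − 2 = 6 degrees of freedom.

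**6. Active versus sham.** If the same PiP therapists treat both arms in balance, the variance is 100 × (1 − ICC) × 2/26. At ICC 0.05 the SE is 2.70 against 2.77, so it is not inflated.

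**7. Which therapist term changes the planned test.** The plan tests change from baseline between groups. Assume 24 patients per arm, 6 PiP therapists shared by both PiP arms, 3 UP therapists, and participant and residual variances of 50 each. The change from baseline to week 8 has variance 2 × 50 = 100 per patient.

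- No therapist effect: SE = √(100 × 2/24) = 2.887.
- Therapist intercept constant over time, variance 5 or 10: it is in both baseline and week 8 and subtracts out, so SE stays 2.887.
- Therapist effect present only after baseline, variance 5: SE = √(8.333 + 5 × (1/6 + 1/3)) = √10.833 = 3.291.

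The second case also fits the design poorly: the Outcomes section measures baseline just before treatment begins, when the therapist cannot yet have had an effect.

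**The case against.** The strongest reply is that nothing in the article shows the ICC to be above zero. It gives no ICC, therapist count or caseload. With a small ICC and many therapists the effect is slight (3% on the SE at ICC 0.01 with four therapists per approach). This stands. A reader might infer that the standard errors are certainly too small, and the documents support only the conditional statement.

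A reader might also apply a caseload of 8 within every compared arm, which gives design effects of 1.14, 1.35 and 1.70 and type I errors of 6.6%, 9.2% and 13.3%. That overlooks the division of a PiP therapist's patients between the active and sham arms.

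Third, a reader might suppose that adding a plain therapist random intercept settles the matter. It does not, because step 7 of the working shows that it leaves the group × time contrast unchanged.

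The sponsor can fairly say that separate sites guard against contamination, that UP is meant to be pragmatic, and that variable PiP delivery is disclosed, with expert support and logbooks as mitigation. These points justify the design but do not address the variance of the contrast. If each approach has a single clinic, clinic coincides completely with approach and no random effect can remove a clinic difference. For that part the remedy is a limit on interpretation.

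The unseen analysis plan is not an answer either. The article states the random-effects structure, and the point concerns what is stated.

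**Conclusion.** The concern holds conditionally. Therapists are in effect nested within PiP or UP, the article expects PiP delivery to vary between clinicians, and the stated model ignores that level. For any post-baseline therapist ICC above zero, the confidence intervals and p-values of both PiP-versus-UP contrasts are anti-conservative.

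At the middle assumption (caseload 8, ICC 0.05), the design effect is about 1.25 and the nominal 5% test runs at about 8.0%. The range over ICC 0.02 to 0.10 is 6.2% to 11.0%. The 87%, 82% and 75% power figures describe a correctly adjusted test under a normal approximation, not the planned test, and would be lower with few therapists. The conclusion does not extend to active versus sham, provided the same PiP therapists treat both arms. This should be corrected before analysis.

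**What to change.** - Add a treating-physiotherapist random effect that acts on post-baseline times. Either a therapist × time random effect in the planned model, or a therapist random intercept in a baseline-adjusted model of the post-baseline outcomes, would do this.
- Use Kenward-Roger or Satterthwaite degrees of freedom.
- Report the therapist ICC and the number of therapists and clinics per approach, which also resolves the uncertainty about how many clinics there are.
- State that, if each approach has its own clinic, clinic cannot be separated from PiP versus UP. Those contrasts then compare services as delivered, and conclusions about PiP itself must be limited accordingly.

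The cost is a small change to the model and a sentence in the limitations. Physiotherapists complete a checklist at every session, so therapist identity should be recoverable. With 28 participants included by December 2025 and follow-up due to end in December 2027, the change can be fixed well before analysis. The price is wider intervals for the two UP contrasts, and a therapist variance that will be imprecisely estimated if therapists are few.
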